### Duration of the project

Specimen collection and processing will last for three years starting in May 2021, unless additional funding has been obtained to expand the biobank. Samples will be stored for fifteen years after collection according to the storage protocol described above.

### Statistical data analysis

In this section, we will describe designs of further studies that we plan to conduct based on the omics data generated from the samples of the biobank.

#### Genome-wide association study of lumbar DD and *in silico* follow-up

We will perform a genome-wide association study (GWAS) using the GCTA software [51] using a mixed model linear regression model and quantitative scales of the assessed disc degeneration status. The GWAS results will be used for replication of genome-wide significant findings from the GWAS of DD conducted in 2013 by Williams et al. [35]. The associations reported by Williams et al. will be considered as replicated if the following two criteria are met: (1) the direction of the effect is the same in both studies; (2) the p-value of association in the replication sample is less than 0.05/4. Further, these two sets of GWAS will be meta-analyzed using the METAL software [52] to obtain the currently largest GWAS on lumbar DD for the European ancestry population. All loci passing the genome-wide significance threshold (p-value < 5e-08) for association will be identified using COJO [53]. The results of the meta-analysis will be used for *in silico* follow-up functional annotation and prioritization of genes involved in lumbar DD development.

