#### Sample size calculation and power estimation

We do not set the upper limit for sample size, although we expect to recruit not less than 1,100 participants and perform a GWAS involving at least 384 patients. Thus, the total sample size of meta-analysis of the GWAS of lumbar DD conducted in 2013 by Williams et al. and in the current study will be about 5,000. This will allow us to detect the genomic loci with an odds ratio of 1.20 or higher with p-value < 5e-8 and 80% power [54].

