#### Functional analysis and data integration

GWAS meta-analysis results will be annotated in order to predict the probable effects of replicated SNPs on gene expression and disease development. Furthermore, we will highlight the molecular pathways, cell and tissue types most likely to be involved in DD pathogenesis using tools like DEPICT [55] and FUMA [56]. This information will be used for gene prioritization alongside the results of the colocalization analysis [57] and Mendelian randomization [58,59]. This methodology will be applied for causal inference between DD and gene expression profiles from different tissues, also including the transcriptomic data from intervertebral discs obtained in this study. A gene network for LDDD regulation will be built and the key regulators will be revealed.

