One more substantial strength of our study is the assessment of the disc degeneration grade by MRI scans, because this is the most accurate and precise method of DD diagnostics. In LDDD studies based on plain radiography [72] or CT [73], phenotype definition is rather subjective as these approaches provide only indirect evidence of disc degeneration such as disc height loss and osteophytes. Similarly, the use of self-reported questionnaires for LDDD identification [74] is not reliable enough. By contrast, the Pfirrmann grading system of disc degeneration used in the present study is based on MRI scans and estimates the main characteristics of DD by assessing the signal intensity and the height of the intervertebral disc: the more dehydrated the disc is, the more severe degenerative changes are in it [42].

This study has some limitations. First, the expected sample size is modest in comparison with national country-level biobanks or large prospective cohorts. The sample size of the present study is one-fourth as large as the one reported for meta-analysis of LDDD studies by Williams et al. [35]. This limitation is explained by funding, establishing the recruitment period of three years. Nonetheless, the expected number of disc tissue samples (~510) and their transcriptome profiles (~40) is comparable with other omics studies using disc specimens (proteome [33]: 7 cases / 7 controls; metabolome [39]: 60 cases / 21 controls; transcriptome [28]: 39 annulus fibrosus (AF) and 21 nucleus pulposus (NP) samples; [29]: 24 AF and 24 NP samples).

The next limitation of our study is an imbalance between patients with “healthy disc” and “degenerated disc” in the group of patients subjected to surgery. Obviously, patients with “healthy discs” are subjected to spinal surgery under specific circumstances. However, according to our protocol, we can still expect some controls in this group (in total, the expected number of controls is 20). In the groups not subjected to surgery, we expect a ratio between cases and controls to be closer to that in the general population.

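### At the guaranteed 384 genotyped patients, the replication rule has only about 18–19% power for a true locus at the genome-wide threshold, so failing it is inconclusive

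*Protocol article*

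**What the plan says.** In the section on the genome-wide association study and its in silico follow-up, the protocol plans a mixed-model GWAS on "quantitative scales of the assessed disc degeneration status" and uses it to replicate the genome-wide significant findings of the 2013 GWAS. Two criteria must both be met: "the direction of the effect is the same in both studies", and "the p-value of association in the replication sample is less than 0.05/4". The two data sets are then meta-analysed, and loci are identified at p < 5e-8.

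Under Sample size calculation and power estimation, the authors say they will "perform a GWAS involving at least 384 patients". The same floor appears under Patient selection and expected sample size. They add "We do not set the upper limit for sample size", and the meta-analysis total "will be about 5,000". The only power figure, 80%, is for that meta-analysis.

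The limitations part of the Discussion states: "The sample size of the present study is one-fourth as large as the one reported for meta-analysis of LDDD studies". Functional analysis and data integration annotates the meta-analysis results in order to "predict the probable effects of replicated SNPs on gene expression and disease development".

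**The concern.** The rule tests each earlier association separately, at a Bonferroni-type threshold, in a sample that may be about one-twelfth the size of the one that produced the finding. A locus that only just reached genome-wide significance in more than 4,000 people cannot be expected to give strong evidence in 384. The Discussion's size comparison will not alert the reader, because it uses the number recruited rather than the number guaranteed for genotyping.

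If failure to meet the rule were reported as a finding about the earlier loci, real loci could be presented as not holding up in this population. Because the functional section refers to replicated SNPs, such loci could also be passed over in annotation.

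**Working it through.** The plan gives no power for the replication step, so there is no figure of its own to reproduce here. The check works on the z scale and needs no odds ratio or allele frequency.

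**Inputs**
- Replication n: 384, the guaranteed floor; 1,100 if everyone recruited were genotyped.
- Earlier sample: 4 × 1,100 = 4,400 (Discussion), or 5,000 − 384 = 4,616 (sample size section).
- Threshold: 0.05/4 = 0.0125. Sidedness is not stated; taken as two-sided, the critical z is 2.498.
- Earlier threshold: 5e-8 two-sided, z = 5.451.
- Assumption: the variant explains the same share of trait variance in both studies.

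**Formulas.** Expected z in the replication sample = z_earlier × √(n / N_earlier). Power = Φ(expected z − 2.498). The wrong-direction tail is negligible.

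**Threshold effect, n = 384**
- N = 4,400: 5.451 × √(384/4,400) = 1.61; Φ(1.61 − 2.498) = 18.7%.
- N = 4,616: 5.451 × √(384/4,616) = 1.57; Φ(1.57 − 2.498) = 17.7%.

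**Other cases** (range over the two values of N, except the last row)

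| Case | Power |
|---|---|
| Earlier z = 7, n = 384 | 32–33% |
| Earlier z = 8, n = 384 | 43–45% |
| Threshold effect shrunk by 30%, n = 384 | 8–9% |
| Threshold effect, n = 1,100 | 57–59% |
| Effect with 80% power at 5e-8 in 5,000 (z = 5.451 + 0.842 = 6.293), n = 384 | 22.5% |

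For 80% replication power, n = N × ((2.498 + 0.842)/z_earlier)². That is about 1,650 to 1,730 for the threshold effect and about 1,410 for the effect in the last row.

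**What each verdict tells the reader.** With the direction criterion, a null locus passes with probability 0.0125/2 = 0.00625. For a threshold-size locus, a pass has a likelihood ratio of 0.177/0.00625 to 0.187/0.00625, about 28 to 30. A failure has a ratio of about 0.813/0.994 = 0.82, close to 1.

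**Size comparison.** 4,400/1,100 = 4, but 4,400/384 = 11.5 and 4,616/384 = 12.0.

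**Joint alternative.** A score over k independent variants of equal strength has expected z = √k × the single-variant value, against 1.960 at two-sided 0.05.
- k = 4: 2 × 1.57 to 2 × 1.61 = 3.14 to 3.22; power 88–90%.
- k = 4, effects shrunk by 30%: 2.20 to 2.25; power 60–62%.
- k = 2: 2.22 to 2.28; power 60–62%.

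**The case against.** Several points on the other side are sound.

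- **384 is a floor.** No upper limit is set, and the document gives no effect sizes or allele frequencies for the earlier loci. A reader might infer that any true locus fails about four times in five. That holds only at n = 384 and for an effect near the genome-wide threshold; stronger loci do better, as the table shows. Still, 384 is all that is promised, and even at z = 8 a true locus fails more often than not.
- **A pass is informative.** It would be wrong to call the verdict worthless. The weakness lies in the negative result alone, and the protocol does not itself say that failure refutes a locus.
- **Annotation starts from the meta-analysis.** Nothing says that a locus failing 0.05/4 is discarded. The phrase about replicated SNPs only leaves that open.
- **One-fourth is not an error.** It is correct for the 1,100 recruited, and 384 is disclosed elsewhere. What is missing beside it is the ratio that governs replication.
- **Multiplicity.** Because the text says scales in the plural and several MRI measures are collected, a reader might infer that the divisor covers one phenotype only and that false replication is inflated. The document does not support this: it never says what the 4 counts, nor that more than one scale enters the replication test.
- **The analyses are secondary to building the biobank.** That lowers the stakes, but the rule is nevertheless fixed in the protocol.

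**Conclusion.** The point holds in a limited form. At the guaranteed GWAS size, the per-association rule has 18–19% power for a locus at the earlier genome-wide threshold and stays below 50% up to an earlier z of 8. Failing it is therefore inconclusive, while passing it is real evidence. The protocol states neither the power of this step nor how a failure is to be read.

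The figures assume a two-sided 0.0125, the same variance explained in both studies, and an earlier sample of 4,400 to 4,616. Overestimated effects in the earlier study would lower the power; genotyping more than 384 would raise it. The joint-test figures also assume independent signals of threshold size, and the document gives neither the number of loci nor their independence. No error in the multiplicity divisor is established; only the replication trait and the meaning of the 4 are left unnamed.

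**What to change.** 1. Keep the per-variant rule and add one pre-specified, direction-aware joint test: a score of the earlier variants weighted by their published effects, tested at 0.05. Restrict it to independent signals or account for linkage disequilibrium.
2. Report each variant's estimate with its confidence interval, and heterogeneity against the earlier effect.
3. State the power of the replication step at 384. Say that p > 0.05/4 at this size is inconclusive and is not grounds for dropping a locus from annotation.
4. Name the single trait used for replication and say what the 4 counts.
5. Add to the limitations that the guaranteed GWAS sample is about one-twelfth of the earlier one.

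The cost is protocol wording and one further regression, with no new genotyping. The drawback is that the joint test shows whether the set of earlier signals carries over, not which variant does; the per-variant estimates remain for that.

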#### Sample size calculation and power estimation

We do not set the upper limit for sample size, although we expect to recruit not less than 1,100 participants and perform a GWAS involving at least 384 patients. Thus, the total sample size of meta-analysis of the GWAS of lumbar DD conducted in 2013 by Williams et al. and in the current study will be about 5,000. This will allow us to detect the genomic loci with an odds ratio of 1.20 or higher with p-value < 5e-8 and 80% power [54].

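### The claim of 80% power for an odds ratio of 1.20 at p < 5e-8 with about 5,000 subjects does not reproduce, and an odds ratio is not what the planned linear mixed model estimates

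*Protocol article*

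**What the plan says.** The section on sample size calculation and power estimation sets no upper limit on recruitment and commits to "perform a GWAS involving at least 384 patients". Combined with the 2013 GWAS of disc degeneration, the meta-analysis total "in the current study will be about 5,000". The power claim follows directly: "This will allow us to detect the genomic loci with an odds ratio of 1.20 or higher with p-value < 5e-8 and 80% power". A source is cited. Allele frequency, case fraction and sidedness are not printed.

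The section on the genome-wide association study describes the analysis itself. It will be run "using a mixed model linear regression model and quantitative scales of the assessed disc degeneration status", meta-analysed with the 2013 results, and read at the same threshold: "All loci passing the genome-wide significance threshold (p-value < 5e-08) for association will be identified using COJO".

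**The concern.** Two things look wrong. First, p < 5e-8 is a demanding threshold, and an odds ratio of 1.20 is a small effect for 5,000 subjects, so 80% power looks too high whatever inputs were used. Second, an odds ratio belongs to a binary or ordinal model, whereas the GWAS section fixes a linear model on quantitative scales. The power sentence therefore does not describe the analysis that will be done.

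This is the only power figure in the article. The meta-analysis it describes feeds the functional annotation, gene prioritisation, colocalisation and Mendelian randomisation. Someone who takes the figure at face value would expect the scan to find most loci of that size, and could give an empty result more weight than it deserves.

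**Working it through.** **Inputs from the article.** Significance level 5e-8, power 80%, odds ratio 1.20, total about 5,000 (all from the sample size section); quantitative trait and linear mixed model (GWAS section).

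**Assumptions, where the article is silent.** The odds ratio is per allele, the test is two-sided and imputation is perfect. Allele frequency p and case share φ are set to their most favourable values and then varied.

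**Step 1. What 80% power requires.** The two-sided critical value is z = 5.451, and 80% power adds 0.842. Required non-centrality = (5.451 + 0.842)² = 39.6.

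**Step 2. Trying to reproduce the claim, binary trait.** Non-centrality = N × φ(1−φ) × 2p(1−p) × (ln OR)², with ln 1.20 = 0.1823 and its square 0.03324. Best case, p = 0.5 and φ = 0.5:

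- 5,000 × 0.25 × 0.5 × 0.03324 = 20.8, against 39.6 needed.
- Power = Φ(√20.8 − 5.451) = Φ(4.558 − 5.451) = 18.6%.
- An allelic test maximised over allele frequency and case share gives 18.5%, as does simulation with 400,000 replicates.
- N for 80% power = 39.6 / (0.25 × 0.5 × 0.03324) ≈ 9,530.

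Other allele frequencies, balanced split:

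| p | Power at OR 1.20, N = 5,000 | N for 80% | OR with 80% power at N = 5,000 |
|---|---|---|---|
| 0.5 | 19% | 9,500 | 1.29 |
| 0.3 | 10% | 11,300 | 1.32 |
| 0.2 | 3.6% | 14,900 | 1.37 |
| 0.1 | 0.3% | 26,500 | 1.52 |

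The last column is exp(√(39.6 / (5,000 × 0.25 × 2p(1−p)))).

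**Step 3. More generous readings of the odds ratio, p = 0.5.** For a graded trait, replace φ(1−φ) = 0.25 by a larger information factor f, so that non-centrality = 5,000 × 0.5 × f × 0.03324:

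- Proportional odds, five equally frequent grades: f = (1 − 5 × 0.2³)/3 = 0.32, non-centrality 26.6, power 38%.
- Proportional odds, continuous limit: f = 1/3, non-centrality 27.7, power 43%.
- Odds ratio converted to latent SD units: 0.1823 × √3/π = 0.1005 SD; non-centrality = 5,000 × 0.5 × 0.1005² = 25.3, power 34%.

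**Step 4. Sidedness and N.**

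- One-sided test (critical value 5.327): 22% binary, 47% in the continuous limit.
- Larger N: the Discussion says "The sample size of the present study is one-fourth as large as the one reported for meta-analysis of LDDD studies". With 1,100 recruits that implies about 4,400 earlier subjects, and 5,500 in total if every recruit were genotyped. The binary best case is then 25%.
- Stacking every concession (N = 5,500, continuous limit, one-sided): non-centrality = 5,500 × 0.5 × (1/3) × 0.03324 = 30.5; power = Φ(5.520 − 5.327) = 58%.

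**Step 5. The planned scale.** For a linear model, non-centrality is approximately N × R², where R² is the share of trait variance explained. 80% power needs R² = 39.6/5,000 = 0.79%. Per allele, β = √(R² / 2p(1−p)): 0.126 SD at p = 0.5, 0.157 SD at p = 0.2 and 0.210 SD at p = 0.1.

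**The case against.** The strongest reply is that the fault may be one of labelling. If 1.20 was a genotype relative risk for a common condition, 80% is reachable. The Introduction puts prevalence at up to 50% in people aged 30–39. With a multiplicative model, a 1:1 split and 5,000 subjects, a relative risk of 1.20 gives about 85% at prevalence 0.3 and allele frequency 0.5. At prevalence 0.5 it gives about 99% at allele frequency 0.2, but only about 67% at 0.1. Likewise, ln 1.20 read as 0.18 SD per allele on a quantitative trait gives 86% at allele frequency 0.15 and over 99% from 0.3 to 0.5. The cited source might settle which was meant, but it is not at hand. This stands as a possible explanation. It does not rescue the sentence: a relative risk of 1.20 at prevalence 0.3 corresponds to a true odds ratio of about 1.30, and an SD effect is not an odds ratio at all.

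It is also fair that the figure drives little. The main aim is to establish a biobank, the Discussion attributes the sample size to funding and calls it modest, and correcting the sentence changes neither recruitment nor the significance thresholds. The unprinted allele frequency and case fraction are not held against a condensed article; they are varied here only to show that no choice of them yields 80%.

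Two stronger readings are tempting, and the article supports neither. A reader might infer that 5,000 subjects give at most 19% power, so that at least four in five such loci would be missed. That ceiling belongs to a binary case-control analysis with a two-sided test, which is not the model planned for the GWAS; graded readings reach 34–43%. A reader might also infer that the quantitative GWAS is underpowered. That does not follow, because the article names no effect on the quantitative scale to judge it against.

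**Conclusion.** Wrong as written. With about 5,000 subjects and a two-sided 5e-8 threshold, power for a per-allele odds ratio of 1.20 is about 19% in the best binary case and about 34–43% on the graded or latent readings, against the stated 80%. Even with N = 5,500, a one-sided test and a continuous graded trait taken together, it reaches only about 58%. These figures assume perfect imputation and the most favourable allele frequency, so realistic values are lower. Separately, the odds ratio is not the effect measure of the linear mixed model in the GWAS section. The conclusion concerns the printed power statement; it is not a judgement on the adequacy of the quantitative analysis.

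**What to change.** Replace the power sentence in the sample size section with one on the planned scale, for example:

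> With N about 5,000 and p < 5e-8 (two-sided) there is 80% power for a variant explaining about 0.79% of trait variance (0.126, 0.157 and 0.210 SD per allele at minor allele frequencies of 0.5, 0.2 and 0.1).

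If an odds ratio is kept as an illustration, state about 1.29 (frequency 0.5) to 1.52 (frequency 0.1), and say that it assumes a balanced binary trait. If 1.20 was meant as a relative risk or as another quantity, name that quantity and its assumptions.

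The cost is one reworded sentence. No patients, genotyping or thresholds change; the price is a less favourable statement of what the meta-analysis can detect.

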#### Functional analysis and data integration

GWAS meta-analysis results will be annotated in order to predict the probable effects of replicated SNPs on gene expression and disease development. Furthermore, we will highlight the molecular pathways, cell and tissue types most likely to be involved in DD pathogenesis using tools like DEPICT [55] and FUMA [56]. This information will be used for gene prioritization alongside the results of the colocalization analysis [57] and Mendelian randomization [58,59]. This methodology will be applied for causal inference between DD and gene expression profiles from different tissues, also including the transcriptomic data from intervertebral discs obtained in this study. A gene network for LDDD regulation will be built and the key regulators will be revealed.

#### Glycomics data analysis

The association of plasma N-glycans levels with disc degeneration status will be studied. We are planning to analyze the differences in N-glycosylation patterns between patients with and without LDDD utilizing machine learning approaches including regression analysis. The results obtained could be helpful for the development of the dynamic glycan biomarkers for elucidating DD pathogenesis and for the development of a prognostic biomarker.

#### Transcriptomic data analysis

The patient group with available intraoperative disc material (see Fig 1) could be divided into “cases” or “degenerated disc” (grades 4–5 of disc degeneration according to the Pfirrmann classification) and “controls” or “healthy disc” (grades 1–3 of disc degeneration according to the Pfirrmann classification) [44,60].

This division does not influence the scheme of patient recruiting or sample collection but plays a role in the transcriptomic data analysis. The groups will include following ICD-10 codes: M51.1 “Thoracic, thoracolumbar and lumbosacral intervertebral disc disorders with radiculopathy” (cases); M51.3, M51.8 “Other thoracic, thoracolumbar and lumbosacral intervertebral disc degeneration” (controls).

Transcriptomic data obtained in this study will be used for detection of genes differentially expressed in discs between cases and controls. In short, the gene expression data will be mapped [61] onto the reference genome and the quality of the reads will be recalibrated (“Picard Toolkit.” 2019. Broad Institute, GitHub Repository. http://broadinstitute.github.io/picard/; Broad Institute). Subsequently, aiming to reveal the transcriptomic differences in intervertebral discs tissue between cases and controls, we will count the reads and identify differentially expressed genes (DEGs) using the edgeR package [62]. To assess the statistical significance of the results, we will apply a Benjamini-Hochberg correction for multiple testing [63]. DEGs will be filtered by the q-value < 0.05 and divided into up- and down-regulated genes. Finally, the revealed DEGs will be functionally annotated with Gene Ontology terms.

The data will also be used to identify expression quantitative trait loci (eQTLs). We will perform an eQTL analysis of gene expression levels in intervertebral discs using the methodology described in [64]. Resulting regional association summary statistics will be used for gene prioritization.

